#### Outcomes

Post-randomisation outcome data will be collected from households: (1) where 24-h mean PM_2.5_ levels are 35 μg/m^3^ or above (we envisage approximately 75% (*n* = 30) households per cluster) and (2) in a small random sample of households where 24-h mean PM_2.5_ levels are below 35 μg/m^3^, as described in the ‘Sample size’ section.

##### Primary outcome

The primary outcome will be 24-h mean household indoor SHS concentration measured as fine particulate matter less than 2.5 μm diameter (PM_2.5_) at 12 months post randomisation.

PM_2.5_ will be measured in homes using the Dylos DC 1700 (Dylos, Riverside, CA, USA) a low-cost particulate counter validated for use in domestic settings [29]. Data from smokers’ homes in Scotland suggest that there is little difference between PM_2.5_ levels measured on the first day compared with levels measured over the following period of up to 6 days. This suggests that installation of these monitors for 24 h will provide a good representation of SHS levels within that home.

*Setting up the Dylos*: 24-h mean PM_2.5_ concentrations will be calculated for each household before randomisation, and at 3 and 12 months post randomisation. Within each household, the Dylos will be plugged into the electricity mains in the living area of the house (excluding the kitchen) most commonly used by family members, at least 1 m away from any doors, windows, or obvious potential sources of PM_2.5_. The Dylos will be switched on to start the logging process at the beginning of each data collection period and will be left to measure and log 1-min particle number concentrations for the duration. The monitors will be supplied with 6-h backup batteries in case of power cuts or brown-outs. Devices record IAQ every minute and enable estimation of SHS concentrations with 1-min resolution over the sampling period. The team is aware of the sensitivities of measuring IAQ in homes and has experience of doing so in various LMICs including Mexico, Pakistan, Indonesia, Chad, Bangladesh, and India [30]. The team will work closely with local partners to ensure that gender and cultural practices are respected.

*Analysing data from Dylos*: data from the Dylos machine will be downloaded to a desktop portable computer at the ARK foundation in Dhaka using the AFRESH software version 4.2 at the end of each sampling day. Dylos particle number concentrations will be converted to equivalent PM_2.5_ mass concentrations and corrected for non-linearity of response. Entry and exit times for each venue will be matched to the sampling day record sheets and an average PM_2.5_ concentration will be calculated for each household. Feedback graphs (Fig. 2) presenting baseline measurement data will be generated to be used in the IAQ feedback component for arm 1.

##### Secondary outcomes

The following will be measured for the household:SHS concentration measured as 24-h mean PM_2.5_ concentration at 3 months post randomisationSmoking restrictions at home: the level of smoking restrictions at home will be assessed through a questionnaire directed at the adults in the households at 3, 6 and 12 months post randomisation

The following will be measured for each member of the household:Frequency and severity of respiratory symptoms: for participants aged 11 years and over, Part 1 (eight questions) of the validated SGRQ [31] will be used to assess participants’ recollection of their respiratory symptoms over the preceding month at 3, 6, and 12 months postrandomisation. SGRQ is a validated questionnaire and a Bangla translation is available for use. For participants younger than 11, respiratory symptoms will be assessed by another severity scale developed and validated by Chauhan et al. [32] at 3, 6, and 12 months post randomisationQuality of life: at 3, 6, and 12 months post randomisation the EQ-5D [33, 34] will be used for adults 18 years and over, EQ-5D-Y [35, 36] for adolescents (11–17 years inclusive) and PedsQoL [37] for children aged below 11 years to measure quality of lifeHealth services use: a health service utilisation questionnaire previously used in the MCLASS pilot trial [19], and adapted to the Bangladesh context, will be used to collect number and type of contacts with physicians, hospital admissions, pharmacy visits and medication prescriptions for all participants. This will be assessed at 3, 6, and 12 months’ follow-up. The MCLASS pilot identified questionnaire items with very low frequency of responses and these questions are omitted from the MCLASS II service use questionnairesMediators of intervention effectiveness: mediators of intervention effectiveness will be quantitatively investigated focussing on those constructs that map onto the intervention logic model that are: attitude, social norms, intentions and action planning, self-efficacy and coping planning with regards to smoking and SHS exposure. These will be assessed at baseline, and at 3, 6, and 12 months’ follow-up using a pre-tested questionnaire, from adults (aged 18 years and over only)

In addition to socio-demographic variables, other confounders identified through the literature a priori will also be measured including:Number of residentsBuilding environmentNeighbourhoodPresence of mould/moisture in homesUse of gas for cooking or gas/kerosene/oil heater.Mosque attendance and receipt/participation in M4bH programmes

The following will be measured for the imams and *khatibs* who will deliver the trial intervention:Pre- and post-intervention training knowledge on smoking and SHS exposure using a semi-structured questionnaire

#### Frequency and duration of follow-up

Data will be collected at baseline, and 3, 6, and 12 months post randomisation as indicated in Fig. 3 below.

**Fig. 3 Fig3:**
[figure not shown]
Data collection schedule

#### Data collection

A total of 16 FIs will screen, recruit households, and collect baseline and follow-up information from 1800 households in 18 months. The FIs will receive 3 days’ training on trial procedures including taking informed consent, administering and completing the questionnaires, delivering IAQ feedback, and ethical issues such as autonomy of households and individual participants on making decisions about participation, freedom to withdraw from the trial without giving any reason or consequence, privacy, confidentiality, anonymity. They will work in pairs during recruitment and baseline data collection for the first few mosques (approximately six mosques) and then work individually with each FI working with one mosque at a time.

Data will be collected using paper-based questionnaires designed specifically for the trial. Collected data will be quality checked and entered into the secure, password-protected database designed specifically for this trial on REDCap (Research Electronic Data Capture), a secure web application for building and managing online surveys and databases (https://projectredcap.org/software/). Collected data will be stored on a central database server.

All data will be stored and transferred following Health Insurance Portability and Accountability Act protocol. The staff involved in the trial will be trained on data protection processes. The staff will be strictly monitored to ensure compliance with privacy standards.

#### Statistical analysis of effectiveness data

##### Analysis of clinical data

The trial will be analysed and reported according to the Consolidated Standards of Reporting Trials (CONSORT) guidelines extension for cluster trials [38]. A detailed statistical analysis plan has been prepared and reviewed by an independent Trial Steering Committee (TSC) prior to the completion of outcome data collection. All analyses will be conducted following the principles of intention-to-treat (ITT), including all participating households within clusters in the trial arm to which the cluster was randomised, using two-sided statistical tests at the 5% significance level. Summaries of the baseline characteristics of the clusters, households and participants will be presented by trial arm. Continuous measures will be reported using descriptive statistics (e.g. *n*, mean, SD, median, minimum and maximum) and categorical data as counts and percentages. No formal statistical comparisons by trial arm will be undertaken on baseline data.

Screening recruitment, and retention data for mosques and households will be summarised, and a CONSORT flow diagram produced. Reasons for non-eligibility/participation will be reported, where available. Follow-up and withdrawal rates at each time point will be presented by randomised group, with reasons for withdrawals given where available.

All outcome data will be summarised descriptively by randomised group and time point.

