#### Recruitment

We aim to enrol 45 mosques (15 in each arm) and 1800 households (40 from each mosque catchment area) into the trial.

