#### Randomisation process

Since the M4bH intervention is an ‘educational’ intervention delivered at a group level, this trial is a cRCT where mosques will be randomly allocated to one of the three trial arms.

Mosque, household and participant recruitment, baseline data collection and randomisation of the 45 participating mosques will be conducted over a period of 6 months. Once recruitment has ceased and mosque and household baseline data collection are complete within a particular mosque, the mosque will be randomly allocated 1:1:1 to one of the three arms using minimisation to ensure balance across the groups on the average estimate size of the Friday prayer congregation (≤ 1500/> 1500) and geographical location (wards within the Mirpur area of Dhaka). Random allocation will be performed by a statistician at the University of York not involved in the recruitment of mosques or households, thus ensuring allocation concealment.

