#### Sample size

Baseline air particulate data were considered for the households recruited from the first six MCLASS II study mosques to be randomised into the trial. Of the 240 recruited, 222 households had at least 22 h of PM_2.5_ concentration measurement at baseline, with an average PM_2.5_ of 66.5 μg/m^3^. The United States (US) Environmental Protection Agency (EPS) considers an Air Quality Index (AQI) of 101 (equivalent to 35 μg/m^3^) or more to indicate unhealthy levels of air pollutants for sensitive groups such as children and the elderly (https://airnow.gov/index.cfm?action=aqibasics.aqi) [28]. Eighty percent of the 222 households at baseline had an average 24 h PM_2.5_ of 35 or more; among these households the mean (standard deviation; SD) was 75.9 (44.2) μg/m^3^.

We propose to recruit 45 clusters (mosques) and 40 households with at least one resident smoker per cluster, and shall follow up up to 30 households per mosque with average baseline PM_2.5_ of 35 μg/m^3^ or more. If there are more than 30 households in the mosque with average baseline PM_2.5_ of 35 μg/m^3^ or more, then 30 will be randomly selected for PM_2.5_ follow-up at 3 months, with randomly selected reserves for those households that are lost to follow-up at this time. If there are less than 30 households in the mosque with average baseline PM_2.5_ of 35 μg/m^3^ or more, then the shortfall will be made up of randomly selected households with PM_2.5_ under 35 μg/m^3^. The same households followed up at 3 months will be contacted for follow-up again at 12 months. We shall assume a 20% attrition rate at 12 months (the primary time point).

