#### Budget impact analysis

A budget impact analysis will be conducted using secondary data to calculate the number of households who might benefit from the implementation of the M4bH intervention, both with and without feedback, and the associated cost of monitors. Based on estimates of the numbers of households, the budget impact of providing the M4bH intervention to all households who might benefit, both with and without a monitor, will be estimated. This component is important as it will demonstrate the potential cost which would be taken into account when assessing the affordability of intervention rollout.

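### The intention-to-treat statement covers all participating households, but only about 30 of 40 per mosque are followed, and the 12-month set depends on being followed at 3 months

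*Protocol article*

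**What the plan says.** **Enrolment and allocation.** Recruitment: "We aim to enrol 45 mosques (15 in each arm) and 1800 households (40 from each mosque catchment area) into the trial". Under Randomisation process, each mosque is "randomly allocated 1:1:1 to one of the three arms using minimisation", once its recruitment and baseline data collection are complete.

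**Analysis population.** Analysis of clinical data commits every analysis to intention-to-treat principles, "including all participating households within clusters in the trial arm to which the cluster was randomised". The Data collection section likewise describes field staff gathering baseline and follow-up data on 1,800 households.

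**Who is followed.** Sample size: the trial "shall follow up up to 30 households per mosque with average baseline PM_2.5_ of 35 μg/m^3^ or more". If more than 30 homes in a mosque qualify, a random 30 are taken, with random reserves to stand in for homes lost at 3 months. If fewer than 30 qualify, randomly chosen homes below 35 make up the number. The homes followed at 3 months are the ones contacted again at 12 months. Outcomes: "Post-randomisation outcome data will be collected from households: (1) where 24-h mean PM_2.5_ levels are 35 μg/m^3^ or above", plus a small random sample of lower homes. That sentence covers outcome data in general, not PM2.5 alone. The IAQ feedback section describes the same restriction.

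**Blinding.** Contamination and risk of bias states that outcome collection and analysis are not blinded.

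**The concern.** Two statements about who is analysed cannot both be true. If the report repeats the intention-to-treat sentence, readers will take the effect and the cost per QALY to describe every enrolled smoker household, when a quarter of them were never meant to give an outcome. The aim, the household eligibility criteria and the cost-effectiveness section carry no PM2.5 restriction that would correct this impression.

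The replacement rule matters more for bias. A home drawn for follow-up and missed at 3 months gives way to a reserve and, as the text reads, is not approached for the primary endpoint at 12 months. Being missed at 3 months can be related to the arm, because households know their allocation and so do the staff who measure them. An analysis set shaped by that event no longer has the protection of randomisation that the intention-to-treat label claims.

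**Working it through.** **1. Homes without outcomes.** Inputs: 45 mosques and 40 homes each (Recruitment); 30 followed per mosque (Sample size).
- Enrolled: 45 × 40 = 1,800. Followed: 45 × 30 = 1,350.
- Not followed by design: 1,800 − 1,350 = 450, and 450/1,800 = 25%.
- The primary model takes PM2.5 at 3 and 12 months as outcome and baseline PM2.5 as covariate. A home with neither later value contributes nothing to it.

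**2. The plan's own power.** Inputs from Sample size: 15 mosques per arm, 30 homes followed, 20% attrition, ICC 0.02, difference 13.5, SD 45, two-sided 5%.
- Homes per mosque at 12 months: 30 × 0.8 = 24.
- Design effect: 1 + (24 − 1) × 0.02 = 1.46.
- Effective n per arm: 15 × 24/1.46 = 246.6.
- Effect size: 13.5/45 = 0.3.
- Power: Φ(0.3 × √(246.6/2) − 1.96) = Φ(1.37) = 91.5%. With a t reference on 28 or 42 degrees of freedom it is 89.5% or 90.2%.

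The stated 90% is reproduced from the followed homes. Following all 40 (32 after attrition) would give about 95.5%, if the SD of 45 also held in all homes, which the article does not say. The sample size was therefore built on the restricted set, and correcting the wording changes no power figure.

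**3. Who is left out.** The Outcomes section expects 75% of homes at or above 35; the Sample size section observed 80% of 222. Assume the number qualifying in a mosque is Binomial(40, p), with no variation in p between mosques.

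| Average per mosque | p = 0.75 | p = 0.80 |
|---|---|---|
| Followed, at or above 35 | 28.9 | 29.7 |
| Followed, below 35 (top-up) | 1.1 | 0.3 |
| Not followed, below 35 | 8.9 | 7.7 |
| Not followed, at or above 35 | 1.1 | 2.3 |

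The followed set is thus mostly, not wholly, high homes, and the omitted set mostly, not wholly, low homes. The implied baseline mean of low homes is (66.5 − 0.8 × 75.9)/0.2 = 28.9 μg/m³, against 75.9 in high homes. Over 45 mosques the top-up gives about 15 (45 × 0.323) to 49 (45 × 1.083) low homes, too few to say much about the effect below 35.

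**4. The 3-month dependence.** Of 1,350 drawn homes, 20% attrition is 270, leaving 1,080 at 12 months. The article does not split this loss by time. The number already missed at 3 months, and so dropped from the 12-month approach, could lie anywhere from 0 to 270 if total attrition is as planned. Reserves are mentioned only for mosques with more than 30 qualifying homes. The last row of the table gives the average pool: 1.1 to 2.3 per mosque, or about 49 (45 × 1.083) to 105 (45 × 2.323) homes in all.

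**The case against.** The strongest reply is that the plan speaks of intention-to-treat principles, and that keeping each followed home in its mosque's arm meets them. The threshold is measured before randomisation, applied alike in all arms, and baseline PM2.5 is in the model. The restriction is disclosed in three sections and the power rests on it. Exact analysis sets may be defined in the statistical analysis plan, which exists but is not shown. Most of this stands, and it confines the first part of the point to wording and scope. It does not remove the contradiction, because the article goes on to say which households are included. It also does not touch the replacement rule, which acts after randomisation.

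A reader might infer more than the documents support:
- **That the baseline selection biases the comparison of arms.** It does not, for the reasons just given.
- **That the planned effect is overstated for all homes.** The difference of 13.5 is tied to a fall from 76 μg/m³, the mean of the high homes, and is nowhere quoted for all homes.
- **That the budget impact assumes benefit in every home.** The text refers to the "budget impact of providing the M4bH intervention to all households who might benefit", which leaves room for a restriction.
- **That homes below 35 should be credited with no benefit.** Nothing in the article supports a zero effect there.
- **That the follow-up list is known to be drawn after allocation.** The article does not say when it is drawn.

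**Conclusion.** The point holds in this form. The intention-to-treat sentence and the reference to follow-up of 1,800 households contradict the follow-up rule: 450 of 1,800 homes (25%) have no outcome by design. The arm comparison and the 90% power are not affected by the baseline restriction, but the effects and cost-effectiveness ratios apply mainly to homes with baseline PM2.5 of 35 or more. Separately, replacing homes lost by 3 months and carrying forward those followed at 3 months makes the 12-month set depend on a post-randomisation event in an unblinded trial. The direction and size of any resulting bias cannot be worked out from the article. This second part rests on reading the sentence about re-contact at 12 months as it stands, that is, as not including homes missed at 3 months.

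**What to change.** 1. Correct Analysis of clinical data and Data collection so that the intention-to-treat set is the households drawn for follow-up under the baseline rule in Sample size.
2. Have the statistician who performs the allocation, and who takes no part in recruitment, draw that list with ordered reserves before the mosque is allocated. Baseline is complete by then. For mosques already allocated, record when and by whom the list was drawn.
3. Keep every drawn home in its mosque's arm, and attempt its 12-month measurement even if it was missed at 3 months.
4. Report reserve homes separately or in a sensitivity analysis.
5. State that effects and cost-effectiveness ratios apply mainly to homes with baseline PM2.5 of 35 or more.

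If the statistical analysis plan already does part of this, align the article with it. The cost is a narrower stated scope and slightly more follow-up administration. No further households need to be recruited and the sample size does not change.

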##### Primary analysis

Twenty-four-hour mean household PM_2.5_ at 3 and 12 months post randomisation will be compared between the groups using a linear covariance-pattern mixed model incorporating the two post randomisation time points and controlling for pertinent baseline covariates at the household and cluster level (including baseline PM_2.5_ value (household-level) and the factors used in the minimisation (cluster-level)). Clustering at the mosque level will be accounted for using a random effect. The correlation of observations within households over time will be modelled by a covariance structure. The mean difference at 12 months will serve as the primary outcome, and the difference at 3 months as a secondary outcome. Residuals will be checked for normality and transformations for the PM_2.5_ data (e.g. log) will be considered. Parameter estimates and corresponding 95% confidence intervals will be presented.

We hypothesise that a combination of the M4bH intervention and IAQ feedback is more effective in improving IAQ than usual services. Therefore, the comparison between the M4bH intervention plus IAQ feedback (arm 1) and usual services (arm 3) will serve as the primary comparison, whilst the comparison between M4bH intervention alone (arm 2) and usual services (arm 3), and between M4bH intervention plus IAQ feedback (arm 1) and M4bH intervention alone (arm 2), will serve as secondary investigations.

##### Sensitivity analyses

To account for non-compliance with the intervention, a complier average causal effect (CACE) analysis [39] will be considered which provides an unbiased estimate of the treatment effect in the event of non-compliance.

##### Secondary analyses

Respiratory symptom questionnaire scores from months 3, 6, and 12 will be analysed in an analogous way as PM_2.5_ concentrations, with an additional random effect for household if feasible. Self-reported smoking behaviour and restrictions will be summarised descriptively per arm.

To explore the potential for mediating mechanisms, the primary analysis model will be repeated, but this time including the mediator of interest as the outcome. The primary analysis will then be repeated including the mediator as a fixed effect. We will be looking for the intervention effect being reduced and the mediator effect being large. Further details including a full list of potential mediators to be explored will be pre-specified and detailed in the statistical analysis plan. These analyses will be exploratory and interpreted accordingly.

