**Discussion:**

The MCLASS II trial will test the potential of a community-based intervention to reduce second-hand smoke exposure at home and improve lung health among non-smokers in Bangladesh and beyond.

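### Home smoking restriction, a named secondary outcome, is only described by arm; it should get a between-arm estimate that allows for mosque clustering

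*Protocol article*

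**What the plan says.** Under Secondary outcomes, the first list is of household measures. It has two entries: PM2.5 at 3 months and smoking restrictions. On the latter, "the level of smoking restrictions at home will be assessed through a questionnaire directed at the adults in the households"; the visits for this are months 3, 6 and 12. The baseline household questionnaire also records restrictions (Participant (and household) baseline assessment).

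Under Secondary analyses the planned treatment of this outcome is one sentence: "Self-reported smoking behaviour and restrictions will be summarised descriptively per arm". Analysis of clinical data already promises descriptive summaries of every outcome by group and time point, so the sentence adds nothing to the default.

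Other outcomes get more. "Respiratory symptom questionnaire scores from months 3, 6, and 12 will be analysed in an analogous way" to PM2.5, that is, with the mixed model. The mediators (attitudes, norms, intentions and similar) are each to be put through the primary model as an outcome, labelled exploratory.

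The primary outcome is "24-h mean household indoor SHS concentration measured as fine particulate matter less than 2.5 μm diameter". The article recognises that particles have other sources. It excludes homes using coal or biomass (Household eligibility criteria), it places the monitor "at least 1 m away from any doors, windows, or obvious potential sources of PM_2.5", and it records gas, kerosene and oil use as confounders.

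For respiratory symptoms the lead-in is "The following will be measured for each member of the household", with a split by age at 11 years and no mention of smoking status. The abstract's Discussion states the hope to "improve lung health among non-smokers in Bangladesh and beyond".

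**The concern.** The interventions aim to stop people smoking indoors. Home smoking restriction is the listed household outcome closest to that behaviour. It is also the only listed household exposure outcome at month 6, because PM2.5 is measured only at baseline and at 3 and 12 months.

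If PM2.5 shows no difference, two explanations compete: smoking rules at home did not change, or they changed and other particle sources hid the effect. Raw percentages by arm do not help much to separate them, because they carry no interval and ignore the 15 mosques per arm. Readers will compare them anyway and will have no honest measure of their uncertainty.

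A softer, related point concerns respiratory scores. Every eligible household has at least one regular adult smoker, while the abstract frames lung health as a matter for non-smokers. An estimate over all members answers a somewhat different question.

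**Working it through.** **1. Is this left to the statistical analysis plan?** For restrictions, no: the article states the analysis, and it is descriptive. For the respiratory population, yes: the article names none, so an analysis in non-smokers may already be planned there.

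**2. Reproducing the plan's own power.** Inputs from Recruitment and Sample size: 15 mosques per arm, 30 followed homes per mosque, 20% attrition, ICC 0.02, effect 0.3 SD, two-sided 5%.
- Homes per arm: 15 × 30 × 0.8 = 360, or 24 per mosque.
- Design effect: 1 + (24 − 1) × 0.02 = 1.46.
- Effective n per arm: 360 / 1.46 = 246.6.
- Standardised difference: 0.3 / √(2 / 246.6) = 3.33. Power = Φ(3.33 − 1.96) ≈ 91.5%; with a t reference on 28 df it is 89.5%. The stated 90% is reproduced, so these inputs are a fair basis for the next step.

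**3. Precision for restrictions.** The Outcomes section limits all post-randomisation data collection to the same followed homes, so 360 per arm applies here too. The article gives no restriction rate and no ICC for this outcome. The rates p of 30% and 50% and the ICC of 0.05 are assumptions; 0.02 is borrowed from the PM2.5 calculation.
- SE of the difference = √(2p(1 − p) / n_eff).
- ICC 0.02, p = 0.5: √(0.5 / 246.6) = 0.0450; half-width 1.96 × 0.0450 = 8.8 points; difference detectable with 80% power 2.80 × 0.0450 = 12.6 points.
- ICC 0.02, p = 0.3: √(0.42 / 246.6) = 0.0413; half-width 8.1 points; 80% power at 11.6 points.
- ICC 0.05: design effect 1 + 23 × 0.05 = 2.15, effective n 167.4. Half-width 1.96 × √(0.5 / 167.4) = 10.7 points at p = 0.5, and 1.96 × √(0.42 / 167.4) = 9.8 points at p = 0.3.

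A fuller two-proportion calculation, taking control rates of 10% to 50%, gives these detectable increases:

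| ICC | 80% power | 90% power |
|---|---|---|
| 0.02 | 8.9 to 12.5 points | 10.5 to 14.4 points |
| 0.05 | 11.1 to 15.1 points | 13.1 to 17.4 points |

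The trial can therefore estimate a change in home rules to within roughly 10 points.

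**4. Respiratory scores.** Let s be the smokers' share of records on the 11-and-over scale and r the smokers' effect as a fraction of the non-smokers' effect. The pooled effect is then 1 − s(1 − r) times the non-smokers' effect. If r = 0, assumed shares of 20% to 50% leave 80% to 50% of it. If r = 1, nothing is lost. Neither s nor r is in the documents, so the size is unknown.

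**The case against.** **Self-report bias.** Outcome collection is not blinded, and in two arms faith leaders have urged people not to smoke indoors. A model cannot remove reporting bias, so a description may seem the honest choice. This stands as a reason for caution in interpretation. It is not a reason to withhold an interval: respiratory scores are also open-label self-report, and the article models them. A description by arm carries the same bias and hides the clustering.

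**PM2.5 already carries the exposure question.** It is modelled at 3 and 12 months, some other sources are excluded or kept at a distance, and randomisation turns the rest into noise rather than expected bias. This stands. A reader might infer that the secondary analyses miss the trial's question about non-smokers. The documents do not support that, and restrictions will at least be reported by arm.

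**Restriction is not the only tobacco-related measure.** Smoking behaviour is to be summarised as well, and the smoking-related mediators are modelled between arms. This also stands. The claim here covers only household-level, tobacco-specific exposure outcomes in the secondary outcome list.

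**Respiratory scores over all members are legitimate.** A reader might call that analysis a contradiction. In the Primary objective, however, the non-smoker wording attaches to exposure and not to respiratory symptoms. The messages also address quit attempts, so smokers may benefit. Nor can a dilution of 20% to 33% be asserted: it assumes one smoker among 3 to 5 respondents, a household size not given, and it pools two age-specific scales. On the under-11 scale the problem hardly arises.

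**Conclusion.** The point holds for home smoking restriction. The protocol fixes a descriptive analysis for a named secondary outcome, while exploratory mediators and equally open-label symptom scores are modelled. A clustered between-arm estimate is a better use of data that will be collected anyway. Its expected 95% half-width is about 8 to 9 points, given 360 followed homes per arm, restriction rates of 30% to 50% and an ICC of 0.02. At an ICC of 0.05 it is about 10 to 11 points. The rates, and the transfer of the ICC from PM2.5 to a reported household rule, are assumptions.

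The gap does not touch the primary analysis. It limits how a null or noisy PM2.5 result can be explained.

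The respiratory part is a suggestion for an added estimate. It is neither a contradiction in the plan nor a reason to replace the all-member analysis.

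**What to change.** **Restrictions.** Replace the descriptive sentence with a between-arm comparison:
- Outcome: full versus not-full restriction, one value per household per visit, with the cut-point and the rule for combining adults' answers set before outcome data are seen.
- Model: mixed logistic over months 3, 6 and 12, with a mosque random effect, repeated measures within household, baseline restriction and the minimisation factors.
- Reporting: estimates with 95% CIs at each visit, ideally also as percentage-point differences. Keep the plan's order of arm comparisons and label the result supportive.

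**Respiratory scores.** Keep the all-member analysis and add an estimate in baseline non-smokers on the 11-and-over scale. Smoking status is already recorded at baseline from age 11.

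**Cost.** Analysis plan wording and some programming; no new data. The trial gains one more secondary estimate resting on open-label self-report, which needs a cautious reading, and its interval will be wider if clustering exceeds 0.02. The non-smoker estimate uses fewer records than the all-member one.
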